#### The PHC-MNCH

We developed the PHC-MNCH system, which comprises a set of sensor devices that were selected based on international information standards and approved by Japanese pharmaceutical law. This sensor set also includes an Android tablet, internet router, and portable printer. The sensors include weighing scales, a digital sphygmomanometer, a blood glucose test sensor, a digital thermometer, pulse oximeters for adults and infants, a height measurement tape, a height measurement mat for infants, a blood hemoglobin meter, and urine test strips. The list of devices is presented in Multimedia Appendix 1.

#### Implementation Team

We created, in advance, a health care worker team that will perform health checkups on participants. The team consists of 2 local residents; one is a qualified paramedic, and the other is a traditional birth attendant. Using the PHC-MNCH system, the team members will act as mediators of health checkup implementation between participant women and physicians.

#### Telehealth Care Intervention

The health care worker team will visit women’s and infants’ homes to examine their health status by using the PHC-MNCH system and conducting interviews to check if they are experiencing any complications. All of the data will be inserted into the triage app installed on the tablet, which will automatically categorize the participants’ health statuses into the following four severity and color levels: healthy (green), cautious (yellow), affected (orange), and emergency (red). Finally, the health care worker team will print out the health checkup reports for women and infants. The women will be remotely connected to a medical physician stationed at Dhaka by using a video system, and they will receive the physician’s consultation on the basis of the results of their checkups, which will be sent through the app. If necessary, the physician will send prescriptions to the women via the health care worker team, using the same app.

#### Health Education

In addition to health checkups, the health care worker team will provide health education to mothers during each home visit through educational videos and brochures, with themes related to antenatal and postnatal care, danger signs in each pregnancy stage, and mothers’ and infants’ nutrition. The education materials were developed based on the regional context of Bangladesh, following a review by a local health expert. The education content is presented in Multimedia Appendix 2.

#### Maternal and Child Health Handbook

The collected health checkup data will be recorded in a physical maternal and child health handbook, so that the information can be kept for future reference. In addition to the health checkup records, this handbook contains health education information regarding perinatal danger signs, infants’ immunization records, and infants’ growth records. The handbook was developed based on the maternal and child health handbook that is presently used in Japan.

#### Health Checkups in the Control Area

Although we will not provide the PHC-MNCH telehealth checkup to the participants in the control area, they can receive any health checkups at any health facilities if they want, as general pregnant women, mothers, and children do in Bangladesh.

### Data Collection Methods and Evaluation

We will assess the impact of the intervention by comparing the clusters, using baseline and end line questionnaire survey data.

#### Baseline and End Line Survey

We will conduct the questionnaire survey at the baseline and end line periods for all eligible women in the intervention cluster and control cluster. The questionnaire items assess sociodemographic and economic status, the health services received and the times they were received, symptoms during pregnancy, and postpartum or neonatal complications. The PHC-MNCH researchers developed the survey in English, and the research assistants translated it into Bengali. A Bengali- and Japanese-speaking researcher then checked the accuracy of the translation.

#### Health Checkup

We will collect the health checkup data of intervention cluster participants throughout the intervention to identify gestational and maternal complication symptoms and health problems. The health checkups will be conducted during 9 home visits, which will be scheduled at approximately 16, 24, 32, and 36 weeks of gestational age and at approximately 2 to 3 days, 7 days, 6 weeks, 6 months, and 12 months after delivery or birth. The measurement- and interview-based checkup items are presented in Textboxes 1 and 2. Health statuses will be categorized into 4 levels according to the criteria developed by Japanese and Bengali obstetricians and medical professionals. Excerpts of criteria details are presented in Multimedia Appendix 3.

With regard to the control cluster, we will not collect health checkup biometric data. This is because conducting health checkups in the control area may affect the mothers’ awareness of health-seeking behaviors and result in bias in the intervention results.

Health checkup items for mothers at different periods.
**Measurements**
All periods from the antenatal period to the motherhood periodWeight, pulse, blood pressure, temperature, hemoglobin, urine protein, urine sugar, oxygen saturation, and blood glucoseAdditional measures for the antenatal periodFetal heartbeat, uterus height, edema, and baby’s position
**Interviews**
Antenatal periodFetal movements, regular contractions, ruptures, vaginal bleeding, smelly vaginal discharge, headaches, vomiting, fevers, convulsions, and depressive symptomsPostnatal periodVaginal discharge, bleeding, uterus hardness, nutrition, nipple problems, perineum tear problems, wound infection, urinating problems, calf pain, headaches, shortness of breath, fevers, convulsions, and depressive symptomsMotherhood periodVaginal discharge, hematemesis, nutrition, nipple problems, headaches, shortness of breath, fevers, convulsions, depressive symptoms, urination problems, urinary leakages, and fecal leakages

Health checkup items for infants at different periods.
**Measurements**
Both the after-birth period and the childhood periodWeight, height, temperature, heart rate, oxygen saturation, cyanosis, and hemoglobin
**Mothers' interviews**
After-birth periodBreathing difficulties, feeding frequency, jaundice, pus, irritated cords, diarrhea, bleeding, and convulsionsChildhood periodBreathing difficulties, pus, diarrhea, hematemesis, convulsions, and the start of complementary feeding

### Study Outcomes and Measurements

The following outcomes will be compared based on the baseline and end line surveys: the frequency of antenatal and postnatal care visits by health care providers conducted through health checkups with the PHC or at health facilities; the detection rate of gestational complication symptoms (suspected gestational diabetes, pregnancy-induced hypertension, anemia, preterm birth, and postterm birth); the detection rate for neonates and infants with suspected jaundice, anemia, and growth delay; the percentage of infants who started complementary feeding at 6 months after birth; and the percentage of participants who sought health care or exhibited health-seeking behaviors or self-care behaviors upon experiencing health problems.

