In Bangladesh, the MNCH status has been improving. However, the maternal and neonatal mortality rates in Bangladesh are still among the highest in Asia; 173 maternal deaths per 100,000 live births and 19.1 neonatal deaths per 1000 live births were reported in 2019 [12]. As a considerable number of maternal and neonatal deaths and gestational complications are avoidable through early health intervention, providing appropriate and continuous care is essential. However, only 44% of women receive antenatal care (≥4 times) from a medically trained health care provider, and 47% of women and 46% of newborns do not receive any postnatal care [13], indicating inadequate MNCH services in Bangladesh. Further, Bangladesh’s cesarean section rate (30.7%) [12], which is higher than the global mean, may be a consequence of insufficient health care, as the cesarean section rate is often considered a proxy indicator of women’s access to care. Several factors have been identified that relate to the lower utilization of MNCH care services, including family wealth, previous experiences of childbirth, autonomy in women [14], and the distance to health facilities [15]. Therefore, financially and physically affordable care needs to be explored further to improve access to care.

Infants’ development status has also been recognized as a problem in Bangladesh; 28% of newborns had a low birth weight in 2015 [16], which was the highest low birth weight rate among newborns in the world at the time. Accordingly, undernutrition in 5- to 9-year-old children was also reported, with 18% of children categorized as *thin* (BMI of <−2 SDs below the mean)—the third highest undernutrition rate among 5- to 9-year-old children in the world. Anemia was also detected among 43% of children aged 6 to 59 months [12]. Hence, children’s nutrition status is also an essential aspect that needs to be monitored at and after birth.

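### The care-uptake outcome counts care outside facilities only when the PHC supplies it, so any switch from other home or community care to the PHC would read as increased uptake

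*Protocol article*

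**What the plan says.** Protocol article, Study Outcomes and Measurements: the first listed outcome is how often women have antenatal and postnatal "care visits by health care providers conducted through health checkups with the PHC or at health facilities". Its source is the questionnaire: "The following outcomes will be compared based on the baseline and end line surveys".

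Protocol article, Telehealth Care Intervention and Health Checkup: the PHC team goes to participants' "homes to examine their health status by using the PHC-MNCH system", and "The health checkups will be conducted during 9 home visits". Four of these are antenatal and five follow birth. Under Implementation Team, the two team members are described thus: "one is a qualified paramedic, and the other is a traditional birth attendant". A physician is linked by video.

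Protocol article, Health Checkups in the Control Area: the PHC is not offered there. Women may use health facilities as they normally would; no other source of care is mentioned.

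Protocol article, Baseline and End Line Survey: the questionnaire covers "the health services received and the times they were received", with no stated limit on place or provider.

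Protocol article, Introduction: the background figure is that "only 44% of women receive antenatal care (≥4 times) from a medically trained health care provider", which is defined by provider and does not mention place.

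Protocol article, Statistical Analyses: effectiveness is judged by a multilevel logistic model of the end line surveys.

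**The concern.** The outcome carries a provider criterion (health care providers) and a route criterion (PHC or facility). The route criterion is not neutral between the areas. A contact in the home counts in the intervention area if the PHC makes it. A contact in the home by any other health care provider counts in neither area.

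If such other contacts occur, a woman who exchanges them for PHC visits has received no more care, yet her counted uptake rises. No equivalent exchange is possible in the control area. The study's aim is to show improved care uptake, so an error in this direction would be reported as benefit.

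This is separate from whether PHC visits should count towards uptake at all. A count limited to facility visits would also drop other home and community care.

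**Working it through.** **Step 1. Which contacts count, on the literal wording**

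| Contact with a health care provider | Intervention area | Control area |
|---|---|---|
| PHC checkup (at home) | counted | not available |
| Visit at a health facility | counted | counted |
| Home or community contact, not PHC | not counted | not counted |

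The third row is excluded equally in both areas, and at baseline. The asymmetry comes from the first row: only the intervention area has a counted route outside facilities that can take the place of the third row.

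**Step 2. When this becomes bias**

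The article gives planning rates only for four or more antenatal visits, so I use that threshold. Let
- p = true share of women with four or more visits, equal in both areas (no real effect);
- h = percentage points of women who reach four visits only if non-PHC care outside facilities is counted;
- s = fraction of those women for whom PHC visits replace that care.

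Counted in control = p − h. Counted in intervention = p − h + s·h. Spurious gap = s·h.

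The gap is zero if h = 0 (no such care) or s = 0 (no replacement). It is h if replacement is complete.

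**Step 3. Would the analysis remove it?**

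No. The stated model compares end line surveys. Subtracting baseline would not help either, because replacement can begin only once the PHC is present, and only in one area.

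**Step 4. Illustrative size**

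Inputs from the article (Sample Size): p = 29%; planned effect 42% − 29% = 13 points; two-sided α = 0.05. I take about 385 women per area, which is 771/2. This reads 771 as a total across both areas, because 771 × 1.2 = 925, the figure given for all clusters. The values of h are assumed, since the article gives none; s is set to 1, its most unfavourable value.

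Share of planned effect = h/13. Chance of a significant false benefit = Φ[(h − 1.96·SE₀)/SE₁], the two-proportion normal approximation, where SE₀ is pooled and SE₁ unpooled. For h = 5 points: control reads 24%; SE₀ = √(2 × 0.265 × 0.735/385) = 0.0318; SE₁ = 0.0318 also; (0.05 − 1.96 × 0.0318)/0.0318 ≈ −0.39; Φ ≈ 0.35.

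| h (points, assumed) | Control reads | Share of planned effect | Chance, no clustering | Chance, assumed design effect of 2 |
|---|---|---|---|---|
| 0 | 29% | 0% | no bias | no bias |
| 2 | 27% | 15% | 9% | 6% |
| 3 | 26% | 23% | 15% | 10% |
| 5 | 24% | 38% | 35% | 20% |
| 8 | 21% | 62% | 73% | 44% |
| 10 | 19% | 77% | 90% | 63% |

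The last column halves the effective number per area to 385/2 = 192.5. The bottom row requires 10/29 = 34% of women with four or more visits to depend on care that the article never mentions. The table shows how the error would scale; it does not predict its size.

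**The case against.** The strongest objection is that nothing in the article shows the uncounted care to exist. Its only description of usual care in the control area is checkups at health facilities. On that account the two named routes may cover everything available, and the wording may simply list the routes expected locally. This stands, and it is why the point is conditional. A reader might infer that control uptake **is** understated; the documents do not support that.

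A reader might also infer that the restriction falls on the control area alone. It does not. It removes non-PHC home care in both areas and at baseline, and bias at end line needs a second condition, replacement by the PHC, which the article does not document either.

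The Introduction's 44% might be read as the study's own definition of antenatal care, contradicted later. It is a cited national statistic, and the outcome also has a provider criterion. The contrast is suggestive, not a contradiction.

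Finally, the article is condensed and the questionnaire is not shown, so provider and place may already be recorded. That bears on how easily the fix can be made. It does not change the outcome sentence, which states the two routes explicitly.

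**Conclusion.** The point holds conditionally. As written, care outside facilities counts only when the study supplies it, and the study supplies it in one area only. If women receive other care outside facilities from health care providers, and PHC visits replace some of it, the end line comparison is biased towards benefit by s·h points.

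Neither h nor s can be obtained from the article, so the size is unknown and may be zero. The chances of a false benefit in the table rest wholly on assumed shares, complete replacement, unchanged true uptake despite four scheduled antenatal home visits, and either no clustering or an assumed design effect. They should not be cited as the trial's error rate.

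The definition still merits correction. If such care is absent, a place-neutral rule changes nothing; if it is present, the current rule distorts the comparison in the direction the study hopes to see.

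**What to change.** In Study Outcomes and Measurements, count every antenatal or postnatal visit by a health care provider, whether at home, in the community or at a facility. Use one written definition of health care provider for both areas and both surveys, and state in it how visits by the PHC team are classed. That statement is needed because the team pairs a paramedic with a traditional birth attendant. Narrowing the term to medically trained providers, as in the Introduction's statistic, would leave open which PHC visits qualify.

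Use the service items in the baseline and end line questionnaires to show PHC visits, other home or community visits, and facility visits separately, so that a reader can see whether one route replaced another.

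The cost is a rewording of one outcome and, if not already collected, a provider and place code on an existing survey item. If the baseline data lack that code, the end line comparison can still be made on the new definition. The downside is small: control uptake may read higher and the apparent effect smaller.

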### Data Monitoring

Data managers will review the accuracy and completion of collected data and thereafter pool them in a project server. Verification checks will be performed to correct any discrepancies in records. Intervention implementation will be monitored by the field monitoring and research team members. All adverse events and unintended effects of the intervention will be reported monthly by the field monitoring team members and followed up by the research team members. Access to all monitoring-related information will be limited to the field monitoring and research team members.

### Participants’ Timelines

The details of participants’ timelines are described in Multimedia Appendix 4. Women will be enrolled at approximately 16 gestational weeks, that is, when they receive the first antenatal checkup. They will be followed up at 9 points in time via health checkups. Infants will be enrolled at birth and followed up at 5 points in time after birth.

### Sample Size

All eligible women and infants at the study sites will be included in our study. Approximately 1000 mother-infant dyads have been deemed eligible for this study among all clusters (500 dyads in each cluster). However, the minimum sample size for recruitment was calculated as 925 dyads for all clusters; 771 dyads in a cluster are required for analyses based on our pilot study, in which the percentage of antenatal care increased by ≥4 times (from 29% to 42%). A 2-tailed test will be conducted (power=0.95; α error=.05). A loss to follow-up rate of 20% was estimated.

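### The sample-size figures (771 per cluster, 925 overall, 500 eligible per cluster) cannot all be true, and 925 less 20% loss falls 31 short of 771 even if 771 is the total

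*Protocol article*

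**What the plan says.** All the figures are in the Sample Size section of the protocol article.

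- Eligible pool: "Approximately 1000 mother-infant dyads have been deemed eligible for this study among all clusters (500 dyads in each cluster").
- Recruitment minimum and analysis requirement: "the minimum sample size for recruitment was calculated as 925 dyads for all clusters; 771 dyads in a cluster are required for analyses", the latter based on the pilot.
- Effect assumed from the pilot: "the percentage of antenatal care increased by ≥4 times (from 29% to 42"%).
- Test: "A 2-tailed test will be conducted", with power 0.95 and alpha 0.05.
- Attrition: "A loss to follow-up rate of 20% was estimated".

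Study Design and Sites fixes what a cluster is. Three villages form the intervention cluster and three form the control cluster, so a cluster is a study arm. Statistical Analyses plans a multilevel logistic model that adjusts for clustering. Sample Size states no design effect or intracluster correlation.

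**The concern.** Three numbers in one paragraph do not fit together. The per-cluster analysis requirement is larger than the number of dyads said to exist in a cluster, and the requirement for both clusters is larger than the recruitment minimum meant to deliver it. Moreover, the one reading that makes the numbers cohere shows a recruitment minimum that does not cover the stated loss.

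The recruitment minimum is a benchmark for judging whether the study enrolled enough. As printed, a reader can conclude either that the study cannot be done at these sites, or that it can reach its minimum and still miss its own analysis requirement. Neither can be settled from the text, because the derivation of 771 is not shown.

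**Working it through.** **Inputs (Sample Size).** p1 = 0.29, p2 = 0.42, difference 0.13, two-sided alpha 0.05, power 0.95, loss 20%, 771 for analysis, 925 to recruit, about 500 eligible per area and 1000 in all.

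**1. Literal reading: 771 per area.**
- Both areas: 2 × 771 = 1542, against 925 to be recruited and about 1000 eligible.
- Per area: 771 − 500 = 271 too few before any loss.
- Allowing for loss: 1542 / 0.80 = 1927.5, so 1928 to recruit.

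This reading is impossible at these sites. Taking a cluster to be a single village would widen the gap.

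**2. Reading 771 as the total.**
- Reproducing the plan's figure: 771 × 1.20 = 925.2, which rounds to the stated 925.
- What 925 delivers: 925 × 0.80 = 740.
- Shortfall: 771 − 740 = 31, and 31 / 771 = 4.0%.
- To retain 771 after 20% loss: 771 / 0.80 = 963.75, so 964 (482 per area).

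The 1.2 multiplier is inferred from the match. The shortfall is not: it follows from the printed 925 and 20% alone, once 771 is taken as the total.

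**3. Does 771 follow from the stated effect, alpha and power?** With mean proportion 0.355, z = 1.960 and 1.645:
- Pooled normal formula: n per arm = [1.960 × √(2 × 0.355 × 0.645) + 1.645 × √(0.29 × 0.71 + 0.42 × 0.58)]² / 0.13² = 349.2. The total is 698, or 700 with whole arms.
- Arcsine: 349.3 per arm, about 699 in total.
- Continuity-corrected: 364.4 per arm, about 729 in total (730 with whole arms).
- Exact Fisher: 365 per arm gives power 0.950, so 730 in total.
- Unpooled variance: 345.6 per arm, 692 in total with whole arms.

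The usual methods therefore give about 698 to 730, or slightly less with the unpooled variance. The stated 771 is 771 / 730 = 1.06 times the continuity-corrected total and 771 / 700 = 1.10 times the pooled total. As a per-arm number it is about twice what is needed. Rounding of the printed percentages could bring the result near 771 (29.5% versus 42% gives 760 by the pooled formula), but that is an assumption.

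**4. What the shortfall costs in power.** Simple individual-level comparison, equal areas, no clustering:

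| Analysed in total | Power, pooled normal |
|---|---|
| 740 | 96.0% |
| 771 | 96.6% |
| 800 (= 1000 × 0.80) | 97.1% |

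With continuity correction or the exact Fisher test, 740 gives 95.3%.

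**5. Effect clause.** 42 / 29 = 1.45, so the rise is 1.45-fold. The four-or-more refers to the number of visits; the Introduction uses the same expression for antenatal care in that sense.

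**The case against.** The strongest defence is that nothing practical turns on this. The section opens by including every eligible woman and infant, so 925 is a floor and not a stopping point. If all of the roughly 1000 take part and 20% are lost, 800 remain, above 771. Even at the floor, 740 analysed meets the 95% power target in a simple comparison. That defence stands as far as it goes, and it limits the size of the point. It does not remove the contradiction, and the power figures ignore the clustering that the planned model adjusts for.

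A second defence is that one phrase is a slip, with a per-cluster label written where a total was meant. That is probably so, but correcting the label alone still leaves 740 against 771.

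Three stronger readings are tempting and not supported:

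- *That the loss allowance was demonstrably applied with the wrong formula.* No formula is printed. The 1.2 multiplier is a close inference, and it depends on first reading 771 as a total.
- *That the study would be underpowered at 925.* The shortfall is against the document's own 771. It is not shown to be a shortfall against 95% power.
- *That 964 is the correct target.* It is correct only if 771 is. Since 771 is not reproduced from the printed inputs, and any clustering allowance in it is unstated, 964 is conditional.

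The effect clause is a wording matter. Both percentages are printed and the meaning can be recovered within the document, so it adds no weight.

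**Conclusion.** The paragraph is wrong as written and needs correcting. As a per-area figure, 771 is incompatible with the 500 eligible per area, the 925 minimum and the roughly 1000 eligible in all. As a total, it is 31 dyads (4%) more than the 740 that remain from 925 after the stated loss. In addition, 771 exceeds the 698 to 730 that the stated effect, alpha and power give, for a reason the text does not state.

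The practical effect is modest. Power at 740 is about 95–96%, and full inclusion of the eligible pool would leave about 800. Those statements assume equal areas, the printed 29% and 42% taken exactly, 20% loss in each area, and no clustering effect. The first part, that the labels are incompatible, rests on no assumption beyond the document's own use of cluster for an area.

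**What to change.** 1. State whether 771 is the total for both areas or the number per area.
2. Show how 771 was derived: the formula or software option, unrounded pilot percentages if they were used, and any allowance for clustering.
3. Divide the confirmed analysis number by 0.80 and restate the recruitment minimum. If 771 is confirmed as the total, this gives 964 in total, 482 per area, which is within the roughly 1000 eligible. If the derivation changes 771, the recruitment minimum changes with it.
4. As a wording note, describe the assumed effect as the percentage of women with four or more antenatal visits rising from 29% to 42%.

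If 771 is confirmed as the total, the cost is a rewritten paragraph and no change to design or conduct. If 771 proves to be per area, or its derivation yields a larger number, the target may exceed the eligible pool, and the plan would then have to say so.

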## Discussion

In our study, the intervention arm participants are expected to have better health statuses than those of the control arm, as they will receive care through the PHC-MNCH. Our community-based intervention study is extremely important for realizing the continuum of care in MNCH through a telehealth care system and evaluating the improvement of mothers’, newborns’, and children’s health status. Previous studies that investigated the effectiveness of the continuum of care in MNCH mostly focused on the perinatal period [20,21]. Through our trial, we will attempt to show whether the continuum of care, which extends from the antenatal period to the motherhood and childhood periods, is effective in improving the health of mothers and infants. The study will further accumulate evidence on the effectiveness of the continuum of care.

Our proposed study also has a limitation. The intervention sites include some of the areas where we conducted the pilot study. Therefore, some residents of the intervention sites may have a better understanding of the continuum of care than those in the control group. However, since the participants in the pilot study are not included in the proposed study, the effectiveness of the intervention will be evaluated based on its status prior to the pilot study. As such, we believe that this limitation can be controlled.

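### The protocol conflicts on whether baseline survey data enter the effect estimate, and the stated power of 0.95 fits only the end-line comparison of the two areas

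*Protocol article*

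**What the plan says.** Sample Size takes its effect from the pilot, "in which the percentage of antenatal care increased by ≥4 times (from 29% to 42"%), and adds "A 2-tailed test will be conducted (power=0.95; α error=.05"). It gives "771 dyads in a cluster are required for analyses based on our pilot study", "the minimum sample size for recruitment was calculated as 925 dyads for all clusters", and "A loss to follow-up rate of 20% was estimated". About 500 dyads per area are thought eligible. The section does not name the contrast being powered, and it gives neither a baseline survey size nor an expected change in the control area.

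On how the effect is judged, the article says two different things.

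- **With baseline data.** Data Collection Methods and Evaluation: "We will assess the impact of the intervention by comparing the clusters, using baseline and end line questionnaire survey data". Study Outcomes and Measurements: "The following outcomes will be compared based on the baseline and end line surveys". The Discussion, on the pilot having run in part of the intervention area: "the effectiveness of the intervention will be evaluated based on its status prior to the pilot study". It concludes from this that the limitation can be controlled.
- **Without baseline data.** Statistical Analyses tests effectiveness with a multilevel logistic model fitted to the end line surveys, with adjustment for clustering. Its earlier step compares the areas for similarity. The Abstract also mentions a generalized estimating equation but does not say which data or which term it uses.

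**The concern.** Villages were allocated purposively, and the pilot ran on the intervention side only. A difference between areas at end line cannot by itself separate the new intervention from a difference left behind by the pilot. The Discussion answers this by referring back to the time before the pilot, but the stated effectiveness model contains no baseline data that could do that work.

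The choice also affects power. A contrast of two end-line proportions carries the sampling error of two cells. A change-against-change contrast carries that of four, and Sample Size makes no allowance for the extra two. If the baseline-referenced contrast became the basis for the conclusion while 0.95 stayed in print, a non-significant result would be read as stronger evidence against the system than it is.

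**Working it through.** **Inputs.** From Sample Size: 29% and 42%, two-sided 0.05, power 0.95, 771 for analysis, 925 for recruitment, 20% loss, about 500 eligible per area. Assumed, because the documents do not give them: independent women (no village effect); 29% in both areas at baseline and in the control area at end line; 42% in the intervention area at end line; and the baseline survey sizes shown below.

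**Analysed number per area.** 771 × 1.2 = 925, so 771 works as a total and gives 771/2 = 385.5 per area. Taking 20% off 925 gives 740, or 370 per area. Taking 20% off 1000 gives 800, or 400 per area. The range used is 370-400.

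**Step 1: the plan's own figure.** For two groups at one time, the variance term is 0.29×0.71 + 0.42×0.58 = 0.2059 + 0.2436 = 0.4495. With a pooled-variance test, power for 29% against 42% is:

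| Per area | Power |
|---|---|
| 370 | 96.0% |
| 385.5 | 96.6% |
| 400 | 97.1% |

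So 0.95 is reproduced to within about 2 points. The number needed for 0.95 is 350 per group (700 in total), or 365 (730) with continuity correction. The exact 771 is not reproduced, but it lies near these totals.

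**Step 2: change against change.** The effect is (42 − 29) − (29 − 29) = 13 points.

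- Risk-difference scale: with n per cell, SE = √[(3×0.2059 + 0.2436)/n] = √(0.8613/n). The variance is 0.8613/0.4495 = 1.92 times that in Step 1.
- Log-odds scale: the effect is ln(0.42/0.58) − ln(0.29/0.71) = 0.573, with variance equal to the sum over cells of 1/[n p(1−p)].
- Power = Φ(effect/SE − 1.96).

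Example at 385.5 per cell: SE = √(0.8613/385.5) = 0.0473; 0.13/0.0473 = 2.75; Φ(2.75 − 1.96) = 78.5%.

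| End line per area | Baseline per area | Risk difference | Log-odds |
|---|---|---|---|
| 370 | 370 | 76.9% | 72.2% |
| 385.5 | 385.5 | 78.5% | 73.9% |
| 400 | 400 | 80.0% | 75.5% |
| 385 | 500 | 83% | 79% |
| 500 | 500 | 87.9% | 84.2% |
| 385 | 1000 | 91% | 88% |

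A simulation of the logistic area-by-period term at 386 per cell gave 74.0%, in line with the log-odds column. Power of 0.95 with equal surveys needs about 662 per cell on the risk-difference scale or 740 on the log-odds scale, against about 500 eligible per area.

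**Step 3: sensitivity to baseline size.** The gap closes as the baseline survey grows. With 385.5 at end line and an unlimited baseline, risk-difference power returns to 96.8%. The baseline size is therefore decisive, and the article does not state it.

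**The case against.** The strongest reply is that Statistical Analyses is the section that fixes the effectiveness test. It uses end line data alone, and 0.95 matches that test apart from clustering. The baseline survey could serve only the similarity comparisons, which would partly fit the wording in Data Collection. This stands as far as it goes: 0.95 is not a miscalculation. It does not account for the Discussion, which says effectiveness itself is evaluated against the pre-pilot state and treats the pilot problem as controlled on that ground.

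A second reply is that the lower figures depend on assumptions. This also stands. Loss to follow-up need not apply to a retrospective survey of past births, so baseline cells may exceed 370-400. In favour of similar sizes, both birth windows under Study Population and Selection Criteria last 48 months, and all eligible women in the same areas are to be surveyed. That makes equal surveys reasonable but does not establish them, so the whole range is shown.

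A third reply is that 771 is printed as a number per cluster, and 771 per cell would give 95.7-97.3% even for the four-cell contrast. That reading does not fit a recruitment minimum of 925 for all clusters or about 500 eligible per area.

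A reader might go further and infer that the protocol plans a difference-in-differences test and is underpowered for it at 72-80%. The documents do not support that. No section names such a contrast or an area-by-period term, and 72-80% is the low end of a range set by an unstated baseline size.

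**Conclusion.** The point holds as an inconsistency that affects power. Three sections bring baseline data into the evaluation of impact, and one of them depends on it to deal with pilot carry-over; the stated model uses end line data only. The 0.95 covers the end-line two-group contrast (96-97% at 370-400 per area, clustering ignored) and has not been shown for a baseline-referenced one. If the latter means change against change, power runs from about 72% to 91% over the survey sizes tabulated, on the assumptions of independent women, 29% in three cells and 42% in the fourth. Clustering by village would lower every one of these figures, including the 96-97%; that is a separate matter and is not quantified here.

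**What to change.** 1. Reconcile Data Collection Methods and Evaluation, Study Outcomes and Measurements, and the Discussion with Statistical Analyses by stating whether baseline data enter the effect estimate. One option that the collected data allow is to pool both surveys and test an area-by-period term. If the end-line model stays as the sole effectiveness analysis, the Discussion should no longer say that the pre-pilot reference controls pilot carry-over.
2. In Sample Size, name the contrast that the 0.95 covers.
3. If the baseline-referenced contrast is adopted, restate its power together with the assumed baseline survey size and the assumed control-area change, and note that clustering by village would reduce it further.

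The cost is one recalculation and a few sentences. The article places data cleaning and analysis after data collection ends, so this can be settled before any analysis. No extra enrolment is proposed. The downside is that the stated power may become less favourable.
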